### Potential mediators

#### Energy expenditure and physical activity

All women will receive an ActiGraph wGT3X-BT accelerometer to monitor their daily activity and energy expenditure. Using a belt clip, women will wear the ActiGraph on their waist for 21 days after Visit 2 and for 21 days before Visit 3. All devices will be calibrated based on the participant’s anthropometric data and configured for recording. Study staff will encourage women to sync their device daily to a phone application via Bluetooth technology. The application will upload data to a software system called CentrePoint, and only study staff will see the participant’s personal online profile in that system to allow for regular monitoring of compliance. For participants without access to a smartphone or Bluetooth technology, study staff will manually upload their data to hospital computers upon arrival at Visits 2 and 3. Women will receive customized reminder communications asking them to wear their ActiGraph upon request or if study staff observe that the participant is not wearing the device as often as desired. All participants will be blinded, such that no physical activity data can be viewed.

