A recent pilot randomized controlled trial (RCT) tested the efficacy of a digital health support program to improve postpartum behaviors and glucose tolerance testing among women with GDM [15]. Participants received an activity monitor and motivational text messages integrated with their activity data. Although postpartum testing increased and the text messages yielded positive feedback from the participants, there was no significant difference between the control and intervention groups in dietary or physical activity goals achieved, and only 45% of participants completed the program. Another study examined weight loss and physical activity using a 3-month, web-based behavioral intervention amongst overweight or obese women with GDM [16]. The intervention consisted of a pedometer program and nutrition counseling with a sample of 28 Caucasian women and 3 women of Asian descent. Despite the small sample size, engaging postpartum women in behavior modification was challenging. Like previous studies, common barriers including lack of time, no childcare, and difficulty implementing lasting lifestyle changes reportedly affected all stages of the study and contributed to their difficulty recruiting and high attrition rate.

The lack of desired results and inconsistent success with previous studies is likely due to incomplete attention to aligning the type of intervention and intervention intensity to barriers postpartum women have to joining and adhering to lifestyle behavior change. It is evident that efficacious interventions to reduce T2DM risk that women can balance with motherhood remain a goal. Our intervention attempts to address this deficiency by adding more intensity to routine daily activities. New mothers are already engaged in an unavoidable lifestyle modification – they spend much of their time engaged in light-intensity physical activity such as cooking, cleaning, and childcare [17–21]. These same activities alone lower blood glucose [22]. We hypothesize that by increasing the intensity of these usual, daily activities, our intervention aims to maximize and increase energy expenditure to efficiently promote weight loss, an essential step towards reducing T2DM risk.

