## Methods/design

### Specific aims

Compare the efficacy of an intervention focused on intensity modification during daily activities versus standard recommendations on measured weight loss (primary outcome).Evaluate the impact of the intervention on body composition (i.e., % body fat, waist-hip ratio) and biomarkers associated with insulin resistance (i.e., glucose, insulin, HOMA, HbA1c, adiponectin, leptin) and metabolic health (i.e., lipids, blood pressure, hsCRP) (secondary outcomes).Examine energy expenditure and diet as potential mediators to better understand the mechanisms behind greater weight loss in the intervention group (exploratory outcomes).

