### Description of the intervention

Women assigned to the intervention will receive the standard recommendation to engage in 150 min of physical activity per week from their obstetric care provider. They will also receive a pair of ankle weights (2.5 pounds [1.1 kg] per ankle) after randomization during Visit 2 to wear until Visit 3. Study staff will instruct women to wear the ankle weights for 2 h every day during routine daily activities (i.e., childcare, household chores) and document the date, time, and activities completed in a study journal for the duration of the intervention. Women will be reminded and encouraged to send pictures of their study journal via email or text message. Study staff will send reminders as encouragement and appreciation weekly when they send in their journals.

Women assigned to the control arm will receive the standard recommendation from their obstetric care provider to engage in 150 min of physical activity per week. They will not receive a pair of ankle weights to wear after randomization, and they will not complete a study journal. This was selected as the control condition because it is the current standard of care.

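### The energy-expenditure mediator comes only from a waist accelerometer with no stated input for the ankle load, so the load-driven indirect effect is biased toward zero

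*Protocol article*

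**What the plan says.** **Mechanism.** The Background hypothesises that "by increasing the intensity of these usual, daily activities, our intervention aims to maximize and increase energy expenditure", and so promotes weight loss. Under Description of the intervention, the means is a load at the ankle: "They will also receive a pair of ankle weights (2.5 pounds [1.1 kg] per ankle) after randomization during Visit 2 to wear until Visit 3". Women wear it 2 h a day during chores and childcare. Both arms receive the same 150 min per week activity recommendation.

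**Mediator.** The exploratory aim under Specific aims is: "Examine energy expenditure and diet as potential mediators to better understand the mechanisms behind greater weight loss in the intervention group". Under Energy expenditure and physical activity, the source is one device: "All women will receive an ActiGraph wGT3X-BT accelerometer to monitor their daily activity and energy expenditure". Its position and timing are: "Using a belt clip, women will wear the ActiGraph on their waist for 21 days after Visit 2", and again for 21 days before Visit 3. Its set-up is: "All devices will be calibrated based on the participant’s anthropometric data and configured for recording". Table 1 lists the same device as the only data source for energy expenditure and physical activity. No load input, second sensor, heart rate or calorimetry is described.

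**Use.** The Analysis section enters this measure in a longitudinal model with multiple mediators and says the tests matter because they identify the most salient mechanisms of change. The abstract and the Discussion list mediation by energy expenditure among the expected contributions.

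**The concern.** The intervention is meant to act mainly on the energy cost per movement, while the sensor mainly records the amount and vigour of trunk movement. A woman doing the same chore with and without ankle weights would give much the same waist reading, although the first costs more energy. Entering her anthropometric data does not help, because body mass enters in both arms and the ankle load in neither.

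The resulting error differs by arm, since the unrecorded component exists only in the intervention arm. It is therefore a bias in the arm-to-mediator path and not mere noise. What is at stake is the mechanism conclusion. A load effect that truly works through energy expenditure could show a small or null indirect effect beside a large direct effect, and be taken as a sign that ankle weights do not act through energy expenditure.

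**Working it through.** **1. The plan's own figure.** The mediator has no sample-size or precision figure. The trial's sample size reproduces. With d = 0.50, 80% power and two-sided alpha 0.05 (assumed, as the article does not state it), the normal approximation gives 2 × (1.96 + 0.84)² / 0.50² ≈ 63 per group, and the t-test gives 63.8, so 64. With 20% dropout, 64 / 0.80 = 80 per group, N = 160. There is no arithmetic error, and the point does not depend on this figure.

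**2. Size of the quantity sought.** The inputs are the pilot losses of 6.3 and 3.9 lb (Participants) and 190 days (Table 2).
- Difference: 6.3 − 3.9 = 2.4 lb = 1.09 kg.
- Daily energy = 1.09 kg × (kcal per kg) / 190. The energy content of lost weight is an assumption: 5000, 7700 and 9000 kcal/kg give 29, 44 and 52 kcal/day.
- If all of it arises in the 2 h of daily wear, that is about 14 to 26 kcal per hour worn.

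This is the extra expenditure a mediator would have to detect if the load explained the whole pilot difference.

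**3. What a partly load-blind sensor does to the mediation estimate.** Let T be the arm, E the movement-related expenditure, and a the load-driven expenditure in the intervention arm.
- True mediator: M = E + a·T.
- Recorded mediator: W = E + s·a·T, where s is the share of the load cost the sensor records.
- Outcome: Y = b·M + error, so the true indirect effect is a·b and the true direct effect is 0.

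Substituting M = W + (1 − s)·a·T gives Y = b·W + (1 − s)·a·b·T + error. Regressing Y on T and W therefore yields:
- estimated indirect effect = s·a·b
- estimated direct effect = (1 − s)·a·b

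Sample size appears in neither expression.

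**4. Numbers.** Set a·b = 0.50 SD, the plan's conservative effect size, with 128 completers. The documents give no value for s, so it is varied. Simulated means for b = 0.3, 0.5 and 0.8 (3000 trials each) agree with the formula:

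| Share recorded (s) | Formula, indirect | Simulated indirect | Simulated direct |
|---|---|---|---|
| 0 | 0.00 | 0.00 | 0.50 |
| 0.25 | 0.125 | 0.12 to 0.13 | 0.37 to 0.38 |
| 0.50 | 0.25 | 0.25 | 0.25 |
| 1 | 0.50 | 0.50 | 0.00 to 0.01 |

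**5. If the load also slows movement.** With s = 0, b = 0.5 and an assumed slowing of 0.1 or 0.2 SD, the indirect effect is 0.5 × (−0.1) = −0.05 or 0.5 × (−0.2) = −0.10 SD. The sign reverses only under this added assumption.

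**The case against.** **The article is condensed.** The energy equation and device settings may stand in a fuller document. That is fair, and their absence is not the point. The article does fix the waist position, the single device and the use of the result as the energy-expenditure mediator. A load term elsewhere could soften the problem, but nothing here indicates one.

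**The intervention may also change movement.** The article calls it activity-boosting, and the intervention arm alone has ankle weights, journals and reminders tied to them. A waist device can detect a resulting change in activity. This stands: the bias concerns the load-driven part only.

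**The aim is exploratory.** The mediators are called potential, and the Discussion leaves robust examination of mechanisms to larger studies. This limits the weight of the point. It does not answer it, because a larger sample leaves this bias unchanged.

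**Stronger readings that the documents do not support.**
- A reader might infer that the indirect effect must be about zero. That needs both a wholly load-driven effect and a sensor that records none of it.
- A reader might infer that weight loss feeds back into the mediator, because a lighter woman is credited with fewer kcal before Visit 3. Table 1 schedules weight only at Visits 1, 2 and 3, so the latest study weight when that window starts is from Visit 2. No conversion equation or later rescaling is stated.
- A reader might infer that the missed effect is credited to diet. Missing one mediator does not by itself create a diet pathway. In the working above the missed part goes to the direct effect.
- A reader might infer that a wrong mechanism conclusion will be published. No section says a null indirect effect would be read as evidence against the mechanism. The risk is that nothing rules that reading out.

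**Conclusion.** The concern holds in limited form. As described, the energy-expenditure mediator has no stated way to capture the extra cost of the ankle load, which is the mechanism the Background puts forward. The load-driven indirect effect is attenuated in proportion to what the sensor misses, and the remainder appears as direct effect.

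The size is unknown, because the documents give no sensor sensitivity. The range from 0.00 to 0.25 of a true 0.50 SD is an illustration for 0% to 50% recorded. It assumes a single mediator, a wholly load-driven effect, and no other measurement error or mediator-outcome confounding. That a waist sensor registers little or none of an ankle load is a general measurement principle and not a statement in the article.

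Only the energy-expenditure part of the exploratory aim is affected. The weight comparison, the secondary outcomes and the diet measure are not.

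**What to change.** Change the wording in Specific aims, in Energy expenditure and physical activity, and in Analysis:

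1. Define the accelerometer mediator as movement volume (counts or active minutes), not converted to energy.
2. State that it tests whether women moved more or less, and not whether the load raised energy expenditure.
3. State that a null indirect effect through this mediator will not be read as evidence against the energy-expenditure mechanism.
4. If a kcal figure is kept, confirm that Visit 2 body mass is used for both wearing windows.

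Adding an assumed kcal-per-hour load term from the wear journals is not a remedy. Only the intervention arm keeps journals, so the term would raise that arm's mediator by construction, and the arm-to-mediator path would be assumed and not tested.

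The cost is wording and a choice of output from recordings already planned, with no new visits or measurements. The downside is a narrower mechanism claim: the trial could speak to changes in movement, but not directly to the energy cost of the load.

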#### Diet

Participants will complete the Diet History Questionnaire III (DHQ III), a web-based food frequency questionnaire based on a collection of national 24-h dietary recall data from the National Health and Nutrition Examination Surveys (NHANES) conducted from 2007 to 2014.

#### Psychosocial assessments

Participants will complete surveys to assess changes in healthy lifestyle habits [24], sleep quality [28], motivation for behavior change [25, 26], perceptions of body shape [27], infant feeding practices, mental health and depressive symptoms [31], and perceived stress [30].

### Analysis

The study will adhere to CONSORT statement guidelines using intent-to-treat as the primary approach for analysis. All individuals will be kept in the group to which they were randomized, regardless of protocol violations or dropouts. Only the pre-specified covariates of baseline outcome variable, race, pre-pregnancy BMI category, GDM severity, parity, clinic location, and education will be included as covariates in the primary and secondary analyses unless imbalances are detected across arms in baseline variables [32]. Balance between the treatment groups will be tested by informally comparing baseline variables between study arms. Outliers will be checked and kept in the final analysis. Outcome variables will also be examined over time at the group and the individual level graphically as well as via descriptive statistics stratified on time and group. No interim analyses or stopping guidelines are planned regarding data monitoring.

Furthermore, bivariate relationships between outcome variables and potential covariates will be examined to determine if substantial deviations from linearity exist. We will make an effort to minimize dropouts and missing data, but if substantial missing data is realized, maximum likelihood estimation will be employed. Although not expected, if substantial non-compliance is realized, modern methods for handling missing data will be utilized [33, 34]. We will continue to collect all outcome data from participants who discontinue the intervention as long as the participant does not formally withdraw and is not lost to follow-up.

Analyses for the primary and secondary outcomes will involve a mixed effects model for repeated measures, similar to ANCOVA but based on maximum likelihood [35]. The same approach, statistical models, and time points (i.e., Visit 2 and 3) used for our primary hypothesis will be used for our secondary hypotheses, with each body composition and biomarker outcome in separate models instead of weight loss. For the Exploratory Aim, we will employ a longitudinal mediation model with multiple mediators. We will use Mplus 7.31 with bootstrapping procedures to statistically test mediators. We will follow the guidelines for testing longitudinal mediation within Cole and Maxwell and MacKinnon [36, 37]. These tests are important for clinical applicability of the intervention by identifying the most salient mechanisms of change that ultimately lead to better outcomes in our target population. Multiple publications will be submitted to peer-reviewed journals to disseminate study results.

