### Participants

Participants will be 160 women diagnosed with GDM during their current pregnancy. GDM is diagnosed with an oral glucose tolerance test using the Carpenter-Coustan criteria [23], typically between 24- and 28-weeks gestation. Testing may occur sooner if a patient has a higher risk of developing GDM.

This sample size was selected based on preliminary data and previous experience from our pilot study. We determined that a sample size of 160 women would be adequate and obtainable due to the number of eligible women we estimate to recruit and enroll, also considering an assumed 20% attrition rate. The recruitment clinics saw 419 unique patients with GDM in 2014. Based on preliminary data and previous experience, we estimate ≥ 80% of those women will be eligible (*n* = 335), of which > 90% will enroll resulting in a potential of *n* = 300/year. Our hypothesis is that women in the intervention will lose more weight than women in the control group. Sample size calculations were based on the difference in the pattern of weight means at study baseline and study endpoint (6-month intervention). Our preliminary data from our pilot studies indicate the intervention group mean weight loss from baseline to month 6 was 6.3 pounds vs. 3.9 pounds in the control group. Using linear mixed effect modeling to detect differences in mean weight change, we estimate an effect size (Cohen’s d) of 0.63. Using a more conservative d = 0.50, we estimate *n* = 64/group (*N* = 128) for 80% power. Assuming a 20% drop out rate, we need *n* = 80/group (*N* = 160), well within the estimated number of eligible women visiting the recruitment sites.

Eligible women will include those that provide written informed consent at 30–40 weeks’ gestation or 7–14 days postpartum, 18 years of age or older, English-speaking, plan to remain in the local area for the duration of the study and are physically capable of engaging in moderate physical activity. Women who are not English-speaking will be excluded because the resources for translating and validating standardized questionnaires for use in other languages are not currently available. Women who have a prior type 1 or type 2 diabetes diagnosis, are surrogate gestational carriers, are pregnant with multiples, deliver prior to 35 weeks’ gestation, have a pre-pregnancy BMI of less than 18.5 (underweight), or live more than 35 miles away from the Ohio State University Wexner Medical Center (Columbus, Ohio) will be ineligible.

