#### Randomization and blinding

Randomization will occur at the end of Visit 2. Research staff determine a participant’s eligibility before Visit 2. A pseudorandom number generator in the statistical software package SAS will be used to implement randomization, stratified by study clinic and BMI group with randomly varying block sizes. [name] will maintain the randomization sequence that will be unavailable to other research study members. Women will be randomized 1:1 to either the intervention or the control condition, stratified by clinic site and BMI category (18.5–24.9 or ≥ 25). The stratifying variables will be entered into REDCap by the research staff, and the concealed randomization algorithm will be programmed in REDCap and used by research staff to randomize women sequentially. Blinding of study investigators, staff, and women will not be possible with this intervention.

There will be five data collection calls. Table 3 shows the timeline for which these calls will be completed and the acceptable windows for these calls to be completed. Table 1 details the measures included in each data collection call.

**Table 3 Tab3:** Data Collection Call Schedule (Moms in Motion Study, Columbus, Ohio, USA)

Data Collection Call	Days Postpartum	Days Post-Randomization
Check-in Call #1: End of Month 2	90 days	60–65 days
Check-in Call #2: End of Month 3	120 days	90–95 days
Check-in Call #3: End of Month 4	150 days	120–125 days
Check-in Call #4: End of Month 5	180 days	150–155 days
Follow-Up Phone Call	360 days	330–340 days

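### The covariate list for the primary and secondary models gives way to informally judged baseline imbalance, so the model and its type I error are not fixed in advance

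*Protocol article*

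**What the plan says.** The covariate rule is one sentence in the Analysis section of the protocol article. It opens with a closed list: "Only the pre-specified covariates of baseline outcome variable, race, pre-pregnancy BMI category, GDM severity, parity, clinic location, and education". It then continues that these "will be included as covariates in the primary and secondary analyses unless imbalances are detected across arms in baseline variables". The next sentence says how imbalance is found: "Balance between the treatment groups will be tested by informally comparing baseline variables between study arms".

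The model to which the rule applies is "a mixed effects model for repeated measures, similar to ANCOVA but based on maximum likelihood", used for weight and, in separate models, for each secondary outcome. The section does not say that the seven-covariate model stays primary if imbalance is found.

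Three other statements bear on the setting. The same section says "Outcome variables will also be examined over time at the group and the individual level graphically", and that "bivariate relationships between outcome variables and potential covariates will be examined", the latter to look for departures from linearity. Under Randomization and blinding: "Blinding of study investigators, staff, and women will not be possible with this intervention".

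**The concern.** The sentence restricts the covariates and then lifts the restriction on a condition that depends on the observed data. Allocation is computer-generated and concealed. If it is carried out soundly, any baseline difference between arms is chance. Adjustment gains precision from covariates that predict the outcome, and the size of a chance difference says nothing about that. Table 1 lists many variables measured by Visit 2, so some difference will probably look notable.

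Two things are at stake. First, the primary model, and every secondary model, is not known until the baseline data have been inspected, so a reader of the results could not tell a planned model from a chosen one. Second, the error rate of the primary test depends on how the exception is applied.

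**Working it through.** **1. The plan's own figure.** The Participants section states: "Using a more conservative d = 0.50", with 80% power, 64 per group, and 80 per group after 20% dropout. The significance level is not stated; I assume two-sided 0.05. Normal approximation: n = 2 × (1.960 + 0.842)² / 0.50² = 62.8, so 63 per group. The exact t-test gives 63.8, so 64 per group (power 0.801). Then 64 / 0.80 = 80 per group, N = 160. The figure reproduces. One-sided 0.05 would give 50 per group, which does not match.

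**2. How often chance alone would show an imbalance.** The article states no threshold, so I use two assumed triggers and 10 independent variables.

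- Absolute standardised mean difference (SMD) above 0.2, 80 per arm: SE = √(2/80) = 0.158. Per variable, 2 × [1 − Φ(0.2/0.158)] = 0.206. At least one of 10: 1 − 0.794¹⁰ = 0.90.
- p<0.05: at least one of 10 is 1 − 0.95¹⁰ = 0.40.

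Correlation among the variables lowers both. With 64 per arm, simulated frequencies for 5, 10 and 20 further variables were about 0.77, 0.95 and 0.998 (SMD trigger) and about 0.23, 0.40 and 0.64 (p<0.05 trigger).

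**3. Type I error.** Simulation of 8,000 null trials per setting with 64 per arm: ANCOVA with seven fixed covariates, plus K further baseline variables that jointly explain a share R² of the residual variance. K, R² and the triggers are assumptions, and ANCOVA on completers stands in for the mixed model. Simulation SE = √(0.05 × 0.95 / 8000) = 0.0024. Results for K = 10, in percent at nominal 5%:

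| Rule | R² = 0 | R² = 0.2 | R² = 0.4 |
|---|---|---|---|
| Fixed list, no exception | 4.7-5.3 | 5.1-5.2 | 5.0-5.1 |
| Add every imbalanced variable, p<0.05 | 4.8 | 4.6 | 4.1 |
| Add every imbalanced variable, SMD > 0.2 | 5.3 | 3.8 | 2.9 |
| Choose among imbalanced variables, keep smallest p, p<0.05 | 5.3 | 5.9 | 5.9 |
| Choose among imbalanced variables, keep smallest p, SMD > 0.2 | 7.0 | 7.9 | 8.9 |
| Any single further variable allowed, keep smallest p | 6.5-7.6 | 9.0-9.1 | 10.2-11.1 |

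Where a range is shown, it covers the runs for the two triggers. Across K = 5, 10 and 20:

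- fixed list: 4.7-5.4%;
- mechanical rule: 4.8-5.3% if the variables are not prognostic, 2.9-4.6% if they are;
- choice among imbalanced variables: 5.2-6.9% with p<0.05, and 6.0-8.9% with SMD > 0.2 for up to 10 variables, approaching 10% at K = 20;
- any single further variable: 6.5-11.1%.

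**The case against.** The strongest reply is that the trigger concerns baseline variables, not outcomes. Read naturally (add whatever is imbalanced), the rule does not inflate the false-positive rate; the table shows it nominal or conservative. The higher rates need an analyst who fits every admissible model and keeps the smallest p, which the article does not propose. The seven fixed covariates include the baseline value of the outcome, and randomisation is stratified by clinic and BMI, so further variables may have little prognostic value left. All of this stands.

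Three stronger readings are tempting and go beyond the text.

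- A reader might infer that imbalance is practically certain. Thirty independent variables would give 1 − 0.794³⁰ = 0.999, or 1 − 0.95³⁰ = 0.79 with p<0.05. But many rows of Table 1 are closely related (glucose measures, lipids, body size), some are already covariates, and neither threshold is in the article.
- A reader might infer that outcome data will steer the choice. The article does not say so. The outcome-covariate checks have a declared purpose, linearity, and the order of steps is simply not given.
- A reader might infer that unblinded people will make the choice. The blinding statement covers investigators, staff and participants with respect to the intervention. It does not say who settles the covariates or whether that person sees arm codes.

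It is also fair to say that a threshold, a candidate list and timing are details an article may leave to an analysis plan, and that the sentence cites a source not available here. The point does not rest on those gaps. It rests on the exception the article does state, which makes the primary model conditional.

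**Conclusion.** The point holds in limited form. The article commits to a closed covariate list and, in the same sentence, lets informally judged imbalance override it for the primary and all secondary analyses, with no unconditional model behind it. The criterion is a poor one, because chance imbalance does not identify prognostic variables, and it is likely to be met by chance: about 90% or 40% for 10 independent variables, depending on the assumed trigger.

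The consequence is a type I error that is not fixed in advance. It is about 3-5% under mechanical use. Under worst-case discretion it is about 6-9% with the wider trigger, or up to about 11% if any single further variable may be chosen. That the 5% rate is certainly lost is not supported. These figures assume two-sided 0.05, independent candidate variables, the stated K and R², and ANCOVA on 64 completers per arm. The change should be made, but the documents do not show harm large or certain enough to call it essential.

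**What to change.** Delete the exception, that is, everything from 'unless' to the end of that sentence, and state that the seven-covariate model is the sole primary and secondary model whatever the baseline comparison shows. Reword the balance sentence so that baseline characteristics are reported by arm descriptively, with no bearing on the model. If adjustment for a striking imbalance is wanted, present it as a labelled sensitivity analysis beside the primary result.

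This is a change of wording only. With the list fixed, the simulated type I error is 4.7-5.4%, nominal within simulation error. The sample size stays at 64 per group, N = 160 with dropout, and the information an imbalance-adjusted model would give is still reported.
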